#### Other reproductive health outcomes

- sexually active last 4 weeks
- current modern contraceptive use (including use of condom, intrauterine device and hormonal contraception) at 4 years follow-up;
- miscarriage and pregnancy termination;
- knowledge of modern contraceptives;

#### Attitudes and beliefs

- perceived community norms regarding education among girls
- perceived community norms regarding modern contraceptive use among unmarried adolescents,
- perceived community norms regarding early marriage,
- perceived community norms regarding adolescent pregnancy

#### Other outcomes

- employment 4.5 years after recruitment;

*Background information to be collected*: household wealth, number of siblings, household members, educational attainment of parents/guardians, age and sex of head of household, number of lifetime sexual partners,.

## Participant timeline

|  | | Time  point | 2016 | | | | | | | | | | | | 2017 | | | | | | | | | | | | | 2018 | | | | | | | | | | | | | 2019 | | | | | | | | | | | | | 2020 | | | | | | | | | | | |  |
| --- | --- | --- | --- | --- | --- | --- | --- | --- | --- | --- | --- | --- | --- | --- | --- | --- | --- | --- | --- | --- | --- | --- | --- | --- | --- | --- | --- | --- | --- | --- | --- | --- | --- | --- | --- | --- | --- | --- | --- | --- | --- | --- | --- | --- | --- | --- | --- | --- | --- | --- | --- | --- | --- | --- | --- | --- | --- | --- | --- | --- | --- | --- | --- | --- | --- | --- |
|  |  |  | | J | F | M | A | M | J | J | A | S | O | N | D | | J | F | M | A | M | J | J | A | S | O | N | D | | J | F | M | A | M | J | J | A | S | O | N | D | | J | F | M | A | M | J | J | A | S | O | N | D | | J | F | M | A | M | J | J | A | S | O | N |
| Enrolment | Recruitment | |  |  | X | X | X | X |  |  |  |  |  |  | |  |  |  |  |  |  |  |  |  |  |  |  | |  |  |  |  |  |  |  |  |  |  |  |  | |  |  |  |  |  |  |  |  |  |  |  |  | |  |  |  |  |  |  |  |  |  |  |  |  |
|  | Eligibility screening | |  |  | X | X | X | X |  |  |  |  |  |  | |  |  |  |  |  |  |  |  |  |  |  |  | |  |  |  |  |  |  |  |  |  |  |  |  | |  |  |  |  |  |  |  |  |  |  |  |  | |  |  |  |  |  |  |  |  |  |  |  |  |
|  | Informed consent/assent | |  |  | X | X | X | X |  |  |  |  |  |  | |  |  |  |  |  |  |  |  |  |  |  |  | |  |  |  |  |  |  |  |  |  |  |  |  | |  |  |  |  |  |  |  |  |  |  |  |  | |  |  |  |  |  |  |  |  |  |  |  |  |
|  | Parent meeting | |  |  | X | X | X | X |  |  |  |  |  |  | |  |  |  |  |  |  |  |  |  |  |  |  | |  |  |  |  |  |  |  |  |  |  |  |  | |  |  |  |  |  |  |  |  |  |  |  |  | |  |  |  |  |  |  |  |  |  |  |  |  |
|  | Parental consent | |  |  | X | X | X | X |  |  |  |  |  |  | |  |  |  |  |  |  |  |  |  |  |  |  | |  |  |  |  |  |  |  |  |  |  |  |  | |  |  |  |  |  |  |  |  |  |  |  |  | |  |  |  |  |  |  |  |  |  |  |  |  |
|  | Allocation | |  |  |  |  |  |  | X |  |  |  |  |  | |  |  |  |  |  |  |  |  |  |  |  |  | |  |  |  |  |  |  |  |  |  |  |  |  | |  |  |  |  |  |  |  |  |  |  |  |  | |  |  |  |  |  |  |  |  |  |  |  |  |
| Interventions | Information meeting for girls, parents and communities | |  |  |  |  |  |  |  | X | X | X |  |  | |  |  |  |  |  |  |  |  |  |  |  |  | |  |  |  |  |  |  |  |  |  |  |  |  | |  |  |  |  |  |  |  |  |  |  |  |  | |  |  |  |  |  |  |  |  |  |  |  |  |
|  | UCT | |  |  |  |  |  |  |  |  | X | X | X | X | | X | X | X | X | X | X | X | X | X | X | X | X | | X | X | X | X | X | X | X | X | X | X | X |  | |  |  |  |  |  |  |  |  |  |  |  |  | |  |  |  |  |  |  |  |  |  |  |  |  |
|  | Payment school fees | |  |  |  |  |  |  |  |  |  |  |  |  | | X |  |  |  |  |  |  |  |  |  |  |  | | X |  |  |  |  |  |  |  |  |  |  |  | |  |  |  |  |  |  |  |  |  |  |  |  | |  |  |  |  |  |  |  |  |  |  |  |  |
|  | Youth club meetings | |  |  |  |  |  |  |  |  | X | X | X |  | | X | X | X |  | X | X | X |  | X | X | X |  | | X | X | X |  | X | X | X |  |  |  |  |  | |  |  |  |  |  |  |  |  |  |  |  |  | |  |  |  |  |  |  |  |  |  |  |  |  |
|  | Community meetings | |  |  |  |  |  |  |  |  | X |  | X |  | | X |  | X |  | X |  | X |  | X |  | X |  | | X |  | X |  | X |  | X |  | X |  | X |  | |  |  |  |  |  |  |  |  |  |  |  |  | |  |  |  |  |  |  |  |  |  |  |  |  |
| Assessments | Baseline interview | |  |  | X | X | X | X |  |  |  |  |  |  | |  |  |  |  |  |  |  |  |  |  |  |  | |  |  |  |  |  |  |  |  |  |  |  |  | |  |  |  |  |  |  |  |  |  |  |  |  | |  |  |  |  |  |  |  |  |  |  |  |  |
|  | Follow-up contacts | |  |  |  |  |  |  |  |  |  | X | X | X | |  |  |  | X | X | X | X |  | X | X | X | X | |  |  | X | X | X | X |  |  | X | X | X | X | |  |  | X | X | X | X |  |  | X | X | X | X | |  | X | X | X | X |  |  |  |  |  |  |  |
|  | Final survey | |  |  |  |  |  |  |  |  |  |  |  |  | |  |  |  |  |  |  |  |  |  |  |  |  | |  |  |  |  |  |  |  |  |  |  |  |  | |  |  |  |  |  |  |  |  |  |  |  |  | |  |  |  |  |  |  | X | X | X | X | X |  |

## Sample size

The sample size is estimated based on the primary outcomes “incidence of births within 8 months of the end of the intervention period” (average age expected to be 17.5 years), “incidence of births before girls’ 18^th^ birthday” and “proportion of girls who sit for grade 9 exam”. We used the 2010 census age-specific estimates of the proportions of 17 and 18 year old girls who ever given birth in the study districts to estimate the proportions in the control arm. The census indicates that 22% of 17 year old and 35% of 18 year old girls in the study districts had ever given birth. Based on this we assume that 27% of girls in the control arm will have given birth before their 18^th^ birthday.

All estimates below have been increased with 10% to compensate for a possible loss to follow up. The sample-size for this cluster-randomized controlled trial was calculated using PASS 14 (NCSS Statistical Software, Utah, US).

*Assumptions for sample size required to measure the primary outcome “birth within 8 months of the end of the intervention period” (*when the average age will be 17.1 years)

| **Parameter** | **Assumed level** | **Comment** |
| --- | --- | --- |
| Incidence of births in control group | 0.06 | Eight months after the end of the intervention period the girls will be on average 17.1 years and we assume that 15% of them will have given birth. This corresponds to an average incidence rate of (15%-3%)/2= 6% over this 2 year period. |
| Effectiveness of combined intervention vs control | -40% | i.e. incidence in combined intervention arm assumed to be 0.036 |
| Cluster size | 28 | See assumptions for the outcome “incidence of births before girls’ 18th birthday” |
| Person years per cluster | 56 | If 28 participants are followed up for 2 years, there will be 56 person years |
| Coefficient of variation (k) | 0.2 | The ICC was 0.00737 for “ever pregnant” after cash transfer trial in Malawi. This corresponds to k=0.20 when the total proportion who have given birth by this time is 0.15 |
| Z_1_ (acceptable alpha error level) | 1.96 |  |
| Power for comparison of combined intervention vs control | 90% | We need 36 combined clusters vs 36 control clusters to have 90% power detect the assumed difference. The PASS function for proportions indicates that with 63 combined clusters, we will have >90% power with 30 control clusters. |
|  |  |  |

*Assumptions for sample size required to measure the primary outcome “birth before 18^th^ birthday”*

| **Parameter** | **Assumed level** | **Comment** |
| --- | --- | --- |
| Incidence of births before girls’ 18th birthday | 0.08 | We assume that 27% of girls in the control arm will have given birth before their 18th birthday. This corresponds to an average incidence rate of (27%-3%)=8% per year over the average 3 year period (from the time the average age is 15). |
| Effectiveness (i.e. (1-RR)×100 of economic intervention vs control | -25% | I.e. the incidence in economic intervention arm assumed to be 0.06 |
| Effectiveness of combined intervention vs control | -40% | i.e. the incidence in combined intervention arm assumed to be 0.048 |
| Effectiveness of combined intervention vs economic intervention | -20% | The combined intervention will offer [1-(0.0.048/0.06)], i.e. 20% more relative protection than the economic intervention alone. |
| Cluster size | 28 | Average number of girls in grade 7 in the selected schools is 31. If we assume that up to 10% may be lost to follow up by the time of measuring the outcome, the average cluster size will be 28 |
| Person years per cluster | 84 | If 28 participants are followed up for 3 years on average, person years per cluster are 84. |
| Coefficient of variation (k) | 0.15 | The ICC was 0.00737 for “ever pregnant” after intervention period in cash transfer trial in Malawi (estimate obtained from [name]). This corresponds to k=0.15 when the total proportion who have given birth by this time is 0.27 [51]. |
| Z_1_ (acceptable alpha error level) | 1.96 |  |
| Power for comparison of economic intervention vs combined intervention | 70% | We need 63 clusters in each of the intervention arms to have 70% power to detect the assumed difference |
| Power for comparison of economic intervention vs control | 80% | We need 39 clusters in each arm to have 80% power to detect the assumed difference. The PASS power calculator for incidence rates does not allow for unequal trial arms, but the PASS function for proportions indicates that 63 economic and 31 control will give slightly higher power^[[5]](#endnote-2)^ |
| Power for comparison of combined intervention vs control | >95% | We need 23 clusters in each arm to have 95% power to detect the assumed difference. |
|  |  |  |

*Assumptions for sample size required to measure the primary outcome ‘proportion of girls who sit for grade 9 exam’*

| **Parameter** | **Assumed level** | **Comment** |
| --- | --- | --- |
| Proportion of girls who sit for grade 9 exam in control arm | 0.70 |  |
| Effectiveness of combined intervention vs control | +26.5% | i.e. proportion completing in combined intervention arm assumed to be 0.886 |
| Effectiveness (i.e. (1-RR)×100 of economic intervention vs control | +15% | i.e. proportion completing in economic intervention arm assumed to be 0.805 |
| Effectiveness of combined intervention vs economic intervention | +10% | The combined intervention will offer a [1+(0.886/0.805)] , i.e. 10% relative increase compared to the economic intervention alone. |
| Cluster size | 28 | See assumptions for the outcome “incidence of births before girls’ 18th birthday” |
| ICC | 0.02 | We have no information on the ICC for this outcome but have assumed it to be higher than for pregnancy |
| Z_1_ | 1.96 |  |
| Power for comparison of economic intervention vs combined intervention | 95% | We need 29 clusters in each of the intervention arms to have 95% power to detect the assumed difference |
| Power for comparison of economic intervention vs control | 95% | We need 24 clusters in each of the arms to have 95% power to detect the assumed difference |
| Power for comparison of combined intervention vs control | >95% | We need 7 clusters in each arm to have 95% power to detect the assumed difference |

Taking the largest of these sample sizes, we need 63 clusters in each of the intervention arms. Since we expect larger differences between each of the intervention arms and the control arm than between the two intervention arms themselves, we can reduce the total number of clusters by allowing for a lower sample size in the control arm. Thus we will include at least 63 economic intervention clusters, 63 combined intervention clusters and 31 control clusters, i.e. 157 clusters with a total of 31 x 157=4867 or approximately 4900 girls..

**Figure 2: Flow chart of trial**

[figure not shown]

## Recruitment

Research assistants will between March and June 2016, i.e. in terms 1 and 2, visit selected schools (with grade 7) and inform girls who are enrolled in grade 7 about the study. The parents/guardians of girls in grade 7 will be invited to an information meeting. If their daughter is < 18 years, they will be asked to give consent to her participation in the trial. A few days later the research assistants will return to the school and ask girls to consent (if they are ≥18 years) or assent (if they are younger than 18 years and their parents or legal guardians have consented) to participation. Those who consent/assent and participate in the baseline survey will be enrolled.

Repeat visits will be made to the school to give girls who are absent on the day of the visit a chance to be enrolled.

Addresses and mobile phone numbers of the girl (if any), parents/guardians and close relatives or neighbours will be recorded when consent/assent is obtained. The girl will be asked to specify the preferred telephone number that can be used to make phone-based follow-up contacts with her.

## Randomization and blinding/masking

Randomization will take place in July 2016, after recruitment and baseline interviews. Randomization will be stratified by district. For each of 6 areas (each area corresponding to 2 districts) approximately 1000 allocations of the clusters will be computer-generated by an independent scientist tasked by CISMAC. Each allocation will be numbered. We will organize six randomization ceremonies where schools will be randomly allocated to one of the three trial arms. Officials from the study districts, head teachers and PTA chairpersons of the trial schools and chiefs will be invited to be present, and others, including community members, will be welcome to come too. Tickets will be drawn from a box with numbers corresponding to a specific allocation of clusters to the three arms.

There will be no blinding of participants, but the team doing the final survey will be independent from the intervention delivery and efforts will be put in place to keep them unaware of the intervention/control status of respondents. Biannual follow-up contacts with the participants and the final surveys will be conducted by an independent team of research assistants, most of them located in Lusaka.

## Data collection methods

A baseline interview will be conducted as part of the recruitment. As part of the trial there will be short phone-based or physical follow-up contacts with all the participants twice per year to update contact details and sociodemographic information. A final follow-up survey will also be conducted. Data will be captured electronically using tablets during face-to-face interviews and using tablets or computers during phone-based surveys and follow-up contacts.

Qualitative and quantitative process evaluation will take place throughout the intervention period in order to understand how the intervention works. Such monitoring activities will also allow identification of needs to make adjustments to the intervention delivery (the intervention will be adaptive [54]). In addition, incentivized lab experiments will be included.

We will collect information about the location and size of pre-randomization non-consenting schools, and information about age and village of girls who do not assent or whose guardians to do not consent, in order to assess the likely degree and direction of selection bias in the study

All the tools will be translated to Tonga, Nyanja, Lenje and Bemba, the dominating local languages in the study districts, and then back-translated to ensure that the content is maintained. Interviews will be conducted in English, Tonga, Nyanja, Lenje or Bemba depending on what the participant prefers.

##

**Table 1: Data collection elements**

| **Activity** | **Description** |
| --- | --- |
| **Baseline survey** | The baseline survey with girls enrolled in grade 7 will consist of interviewer-administered face-to-face interviews and will be carried out at school. We will employ and train a team of research assistants and a supervisor in each district to conduct this survey. The questionnaire is attached. |
| **Monitoring of school attendance** | Attendance reports will be collected at the end of the intervention period for all girls in the trial. |
| **Follow-up contacts** | All the girls in the intervention and control arms will be contacted every 6 months to update contact information and ask questions about school attendance, employment, marital status and childbearing, health care seeking, and whether they have received the cash transfers and/or participated in the youth club meetings. To monitor adverse events that can be attributed to the trial, girls will also be asked whether they have experienced problems due to their participation in the trial. In the fourth follow-up interview (taking place during the first two quarters of 2018) additional questions will be asked about communication about sexual and reproductive health issues.  In order to make it easier for the participants to respond to the more sensitive questions, Audio Computer Assisted Self-Interviewing (ACASI) will be used for questions 69-82. This will be done by giving the participants headsets so they can listen to the questions being read to them and they will be given privacy to fill in the correct responses on the tablets themselves. ACASI-technology has been shown to increase participants’ perceptions of privacy and anonymity and it appears to reduce social desirability bias [52, 53]. In addition, the item count technique [54, 55] will be used. This is an indirect questioning technique where the participants indicate how many of a set of statements are true for them, rather than whether each of the individual statements are true or false. If the girl cannot be found at school or at home at the time of the follow-up interview, call centre research assistants will attempt to reach her by phone.  In the third follow-up round we experienced challenges in several of the control schools with finding the participants because many of them were not in school any more. In order to motivate the participants to come to the school to be interviewed, we will increase the transport allowance provided for control participants from K20 to K50 per interview in 2018 and further to K75 in 2019 and K100 for the final interview in 2020. For the participants in the intervention arms, we do not think it is necessary to provide such an allowance during the period when they are receiving economic support, and thus a transport allowance of K75 / K100 will only be provided for interviews in 2019 and 2020. The participants will then have finished grade 9 and we expect a large proportion of them to move away from the study areas, either to go to grade 10 in a secondary school or to get married or work. This implies that they will either have to travel to come back for interviews and need to be compensated for the costs and time that this requires. And for those that move far away, they will have to keep their phone number active for us to be able to interview them over the phone and many of them will also have to call us to inform us when they will be available, and thus the compensation should be sufficient to cover the costs of this.  Around the time of the fourth follow-up interviews with the RISE participants in the first half of 2018, their parents/guardians will also be invited to come to parent meetings where they will be asked take part in an interview. Parents/guardians who do not come to the meeting will be sought at home. The questions in the parent interview pertain to expenses they have had in the previous 6-12 months related to food, education, health care and other expenditures, and about their attitudes to early marriage, early childbearing, contraceptive use and education. A travel allowance of K50 will be offered to the guardians who are interviewed.  The research assistants will be asked to take selfies of themselves with the participants to document that they have interviewed the correct participants. The trial participants in most cases live far away from each other and the research assistants who do the interviews travel alone (or with a driver) on a motorbike to find the participants. Thus, even if there is a supervisor who makes unannounced monitoring visits to observe the research assistants twice per month, most of the interviews are done without other project staff being able to observe them. We are worried that some of the research assistants may be tempted to manufacture some of the interviews, particularly when it is difficult to find participants because they have moved (which is the case for an increasing proportion of our participants). We expect that such pictures will make fabrication of interviews less likely. |
| **Qualitative process evaluation** | The trial supervisors at district level will be present at 1/6-1/3 of the youth club meetings to observe the quality of the delivery of the community component. They will record their observations and give feedback to the community teams. IDIs and FGDs will be conducted every year during the intervention period to explore experiences of purposively selected participants’ (from within the categories girls, boys, parents/guardians, other community members) with the various intervention components, reasons for non-participation in the intervention, and their perspectives on the accessibility of SRH services. Draft interview guides are attached. |
| **Quantitative process evaluation** | We will collect administrative data on school performance and school attendance of all study participants from school registers in the study districts. In addition to the information obtained about participation in the intervention components during followup contacts, we will also collect attendance list from the each youth club meeting, logs with counts of how many persons show up will also be saved for all parent – and community meetings. We will moreover monitor whether similar activities take place in the control clusters.  In addition, we will design incentivized experiments that will provide unique data on the causal effects of the interventions on the participants’ risk-, time-, and social preferences. These experiments will follow standard protocols in behavioral economics, see for example Almås, Cappelen, Salvanes, Sørensen, and Tungodden (2012) [55]. |
| **Final follow-up survey** | A phone-based final follow-up survey will be conducted in the last quarter of 2020. If the girl cannot be reached via phone, field-based research assistants will attempt to find her. At this point almost all the girls will be more than 18 years. The questionnaire will be developed later and will include measurements of pregnancies, births, stillbirth, premature birth, neonatal mortality. miscarriage and pregnancy termination, employment and salary level, health care utilization, and knowledge of and use of modern contraceptives. If the girl cannot be reached via phone, field-based research assistants will attempt to find her |
| **Case report form** | We will keep an electronic Case report form (CRF) for each participant where we will record information from the eligibility screening, contact information, consent issues, social problems experienced due to the trial, cash transfer issues, reasons for loss to follow-up etc. Information about the attendance in youth club meetings in the community component will be recorded on paper forms and will be entered into the electronic case report form for each participant in the combined intervention arm. Information about cash transfers and payment of school fees will also be recorded electronically and this information will automatically be updated in the electronic case report form. |

It seems that participants who are lost to follow-up are particularly likely to be married, and since we know that marriage is closely associated with early childbearing, we are concerned that loss to follow-up may introduce bias in the measurements of the outcomes related to childbearing and marriage. Thus we are requesting permission to record information about marital status and childbearing of participants who have been lost to follow-up. This information will be used in a secondary analysis of the proportion who has given birth and who are married.

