## Participant population

#### The participant population will be girls enrolled in grade 7 (average age approx. 14 years) in 2016 in rural basic schools in the twelve study districts.

## Eligibility criteria

All girls enrolled in grade 7 in the included schools will be eligible to participate, including those who are already married or have children. Girls without a parent or legal guardian living in the household will also be eligible to participate if the headmaster of their school or the headman of the village gives consent. There will be no age restriction.

Girls who drop out of school after they have been recruited will continue to be part of the trial.

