### *Secondary outcomes:*

#### Pregnancy and childbearing

- proportion of girls who have ever given birth after 2 years of programme implementation;
- proportion of girls who have ever been pregnant after 2 years of programme implementation;
- proportion of girls who have ever been pregnant before their 16^th^ birthday;
- proportion of girls who have ever given birth before their 16^th^ birthday;
- proportion of girls who have ever been pregnant before their 18^th^ birthday;
- socioeconomic equity in proportion of girls who have ever given birth before 18^th^ birthday;

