## Statistical methods

The outcomes will be captured in binary, continuous or a time-to-event variables. Continuous variables that are right skewed will be log-transformed to obtained more symmetrical distributions. We will correspondingly employ Poisson regression or General linear models (GLM) of the binomial family with a log link (estimating risk ratios or RRs) and identity link (estimating absolute risk reduction), linear regression (estimating average effect or mean increase or decrease) or survival analysis using Cox regression. Each method will take account of the design effect of the clustering.

The data will be analysed with Stata (Stata Corporation, TX, USA) statistical software. We will compare outcomes between the three arms: the economic arm vs. the control arm, the combined arm vs the control arm, and the economic arm vs the combined intervention arm. Analyses will be by intention-to-treat (ITT), that is all participants, irrespective of whether they actually agree to the intervention allocated to them, will be included in the analysis according to the intervention arm the cluster they live in was allocated to. The Intracluster correlation (ICC) will be reported for all primary and secondary outcomes.

The primary outcomes will be measured in the final survey in February 2020 based on the participants’ responses to the questions “Have you ever given birth?” and “If yes, on which date and which year did you give birth?”. Reported childbearing before July 2019 will be recorded as “birth 8 months after end of the intervention period”. Girls who report a date of childbearing preceding their 18^th^ birthday, will be recorded as having “birth before 18^th^ birthday”. Girls who are married at the start of the intervention, will be excluded from the analysis of proportion of girls ever married/cohabiting before their 16^th^ or 18th birthday.

Descriptive statistics, such as means or medians and standard deviation or interquartile range will be used to describe continuous variables (the choice depending on the distributions). For categorical variables, frequencies and percentages will be calculated.

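### The protocol's own mean ages do not support almost all girls being over 18 at the final survey, and the age-18 outcomes defined as plain proportions, with their absolute effects, would be understated

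*Protocol*

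**What the plan says.** On timing, Table 1 states: "A phone-based final follow-up survey will be conducted in the last quarter of 2020". It adds that "At this point almost all the girls will be more than 18 years". The Participant timeline and Appendix 1 mark the survey from July to November 2020.

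On age, Participant population describes "girls enrolled in grade 7 (average age approx. 14 years) in 2016", and Eligibility criteria adds "There will be no age restriction". The Sample size table for the first birth outcome says "Eight months after the end of the intervention period the girls will be on average 17.1 years". The opening paragraph of the same section gives 17.5 for that time point. Statistical methods places it at July 2019.

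On the outcomes, the primary outcome is an incidence of births before the 18th birthday, with a sample size in person-years. Statistical methods records as events those fitting "Girls who report a date of childbearing preceding their" 18th birthday, and gives no rule for girls who are not yet 18 and report no birth. Secondary outcomes include "proportion of girls who have ever been pregnant before their" 18th birthday, and socioeconomic equity in the proportion who have given birth before 18. Proportions are to be analysed by binomial GLM, giving risk ratios, absolute risk reductions and numbers needed to prevent.

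**The concern.** A before-18 outcome is fully observed only in a girl followed to her 18th birthday. The sentence in Table 1 implies that this holds for nearly everyone, so no special handling looks necessary. If a sizeable minority are still 17 or younger at last contact, a yes/no flag divides the events seen so far by all girls. The result is then not the risk by age 18.

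At stake are the control-arm proportion, the absolute risk reductions and the numbers needed to prevent. Equity comparisons on the absolute scale are also exposed. If age in grade 7 varies with wealth or parental education, the tertiles differ in how many girls are observed to 18.

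**Working it through.** **Inputs from the protocol.** Mean age in July 2019 of 17.1 or 17.5; survey in July-November 2020 (timeline) or the last quarter (Table 1). For birth before 18: 3% at the average age of 15, then 8% per year in control, 6% in the economic arm and 4.8% in the combined arm; 28 girls and 84 person-years per cluster; k = 0.15.

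**Assumptions.** Ages are normal with SD 0.8 to 1.8 years. The mean is dated 1 July 2019. Survey dates are spread evenly over the window.

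**The plan's own figures.** The rate formula c = 1 + (z_α/2 + z_β)²[(λ0+λ1)/y + k²(λ0²+λ1²)]/(λ0−λ1)² gives 39 and 23 clusters for the two comparisons with control, as stated, and 62 for economic against combined, where the plan states 63. The cluster counts therefore reproduce. The statement about age does not.

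**Share under 18.** This is Φ((18 − mean)/SD), averaged over the window. For example, a mean of 18.43 with SD 1.0 gives Φ(−0.43) = 33%.

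| Mean, July 2019 | Window in 2020 | Mean at survey | SD 0.8 | SD 1.0 | SD 1.4 | SD 1.8 |
|---|---|---|---|---|---|---|
| 17.1 | Jul-Nov | 18.3 | 35.1% | 38.0% | 41.4% | 43.2% |
| 17.1 | Oct-Nov | 18.4 | 29.5% | 33.2% | 37.8% | 40.5% |
| 17.5 | Jul-Nov | 18.7 | 19.1% | 24.1% | 30.8% | 34.8% |
| 17.5 | Oct-Nov | 18.8 | 14.9% | 20.3% | 27.6% | 32.2% |

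Starting instead from age 14 in 2016 gives a mean of 18.4 to 18.9 in mid last quarter, depending on the month to which the 14 applies.

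**Spread needed for the statement.** For 95% over 18, SD ≤ (mean − 18)/1.645. In mid last quarter this is 0.43/1.645 = 0.26 to 0.84/1.645 = 0.51 years from the two July 2019 means, and at most 0.53 from the most favourable age-14 start. For 90% (divisor 1.2816), the two July 2019 means give 0.34 to 0.65. A single-birth-year cohort has SD 1/√12 = 0.29.

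**Person-time and power for the primary rate.** Let T be the mean of min(age, 18) − 15, bounded at 0 and 3. The plan uses T = 3.0. Across the table T runs from 2.45 (first row, SD 1.8) to 2.94 (last row, SD 0.8), so y = 28T is 68.6 to 82.3. Inverting the formula with 63 clusters per arm, power for economic against combined is 71% at y = 84, and 63-70% over that range.

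**Plain proportions.** Control is 3 + 8T and combined is 3 + 4.8T, in per cent.

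| T | Control | Combined | Difference | Ratio | 100/difference |
|---|---|---|---|---|---|
| 3.00 (plan) | 27.0 | 17.4 | 9.6 | 0.644 | 10.4 |
| 2.94 | 26.5 | 17.1 | 9.4 | 0.645 | 10.6 |
| 2.45 | 22.6 | 14.7 | 7.8 | 0.653 | 12.8 |

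The protocol gives no rates for pregnancy, so birth rates stand in for them here.

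**The case against.** The strongest reply is that the primary outcome is an incidence rate. Its sample size uses person-years, Poisson and Cox models are named, the change log records the move of birth measures from proportions to rates, and Cox regression is planned for time to first pregnancy. A girl aged 17 at last contact then contributes the time she was observed. Exact censoring rules may sit in the SAP. All of this stands for the rate and Cox analyses. A reader might infer that the protocol scores every girl under 18 as having no event in the primary outcome. It does not. A girl under 18 who has given birth is an event, and for the others no rule is stated. If the change log is taken to cover the equity-in-birth outcome too, what remains is pregnancy before 18 and the absolute measures.

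A second reply is that the age SD is not in the protocol, and that the consent route for girls aged 18 or more is a procedural provision and says nothing about the actual spread. This is fair. A reader might take a figure such as 30-40% as following from the stated mean and the open age criterion. It does not: it needs an assumed SD, and the stated mean of 17.5 gives lower shares. A skewed age distribution would also change the lower tail. Yet the SD that rescues the sentence is close to that of a single birth year. That fits poorly with open age eligibility, inclusion of girls already married or with children, and a support rule for girls who pass 18 during the intervention.

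A third reply is that the hypotheses are relative reductions and the equity analysis compares effects between tertiles. This also stands: ratios barely move if ages are balanced across arms. Only absolute contrasts shift.

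**Conclusion.** The sentence in Table 1 conflicts with the protocol's own mean ages unless the age SD is about 0.5 years or less. For SDs of 0.8 to 1.8 years, about 15-43% of girls would be under 18 at a survey in July-November 2020. The finding does not depend on the other date in Statistical methods, "The primary outcomes will be measured in the final survey in February 2020". That date would make it worse, with 47-62% under 18 at SD 1.0.

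For the primary birth-before-18 rate, the cost is person-time (2.45-2.94 instead of 3.0 years per girl) and a few points of power, not false non-events. For the age-18 outcomes still worded as proportions, and for absolute risk reductions and numbers needed to prevent, the plan as written understates the figures: control about 22.6-26.5% instead of 27%, and the combined-arm difference about 7.8-9.4 points instead of 9.6. These sizes rest on the assumed SD, normal ages and the plan's constant rates. The point should be corrected, but it does not threaten the main relative comparison.

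**What to change.** 1. Replace the Table 1 sentence with the share expected to be over 18, calculated from the baseline dates of birth. At the same time, reconcile the two mean ages (17.1 and 17.5) and the survey dates.
2. Estimate the age-18 pregnancy and birth proportions, and their absolute effects, from time-to-event data censored at the earlier of the 18th birthday and the last contact, reading the risk at age 18 from the survival curve. This keeps every girl and needs no new data.
3. If a plain proportion is also reported, restrict it to girls whose baseline date of birth puts their 18th birthday before the survey opens. Using the date it closes would keep girls interviewed before they turn 18. The restriction uses baseline data only, so the randomised comparison is preserved.

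The cost of the first two is wording and analysis code. The third loses girls. With opening in July 2020 (mean 18.1 or 18.5), Φ((18 − mean)/SD) drops about 27-48%. With opening in October (18.35 or 18.75), it drops about 17-42%. Intervals widen by 1/√(1 − share dropped), roughly 10-40% before allowing for clustering. The restricted proportion therefore belongs in a supporting role.
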